## Abstract

**Background:**

Tobacco cessation training programs to treat tobacco dependence have measureable effects on patients’ smoking. Tobacco consumption in low- and middle-income countries (LMICs) is high and slowly decreasing, but these countries usually lack measures to face the epidemic, including tobacco cessation training programs for health professionals and organizations. Based on a previous online smoking cessation training program for hospital workers in Spain, the Fruitful Study aims to increase smoking cessation knowledge, attitudes, self-confidence, and performance interventions among health care professionals of three Spanish-speaking low- and middle-income Latin American and Caribbean (LAC) countries.

**Objective:**

The purpose of this paper is to describe the methodology and evaluation strategy of the Fruitful Study intended to adapt, implement, and test the effectiveness of an online, evidence-based tobacco cessation training program addressed to health professionals from Bolivia, Guatemala, and Paraguay.

**Methods:**

This study will use a mixed-methods design with a pre-post evaluation (quantitative approach) and in-depth interviews and focus groups (qualitative approach). The main outcomes will be (1) participants’ attitudes, knowledge, and behaviors before and after the training; and (2) the level of implementation of tobacco control policies within the hospitals before and after the training.

**Results:**

To date, adaptation of the materials, study enrollment, and training activities have been completed. During the adaptation, the main mismatches were language background and content adaptation. Several aids were developed to enable students’ training enrollment, including access to computers, support from technicians, and reminders to correctly complete the course. Follow-up data collection is in progress. We have enrolled 281 hospital workers. Results are expected at the beginning of 2017 and will be reported in two follow-up papers: one about the formative evaluation and the other about the summative evaluation.

**Conclusions:**

There is a need to learn more about the cultural and content elements that should be modified when an online tobacco cessation training program is adapted to new contexts. Special attention should be given to the personal and material resources that could make the implementation possible. Results from the Fruitful Study may offer a new approach to adapting programs to LMICs in order to offer education solutions with the use of emerging and growing communication technologies.

**ClinicalTrial:**

Clinicaltrials.gov NCT02718872; https://clinicaltrials.gov/ct2/show/NCT02718872 (Archived by WebCite at http://www.webcitation.org/6mjihsgE2)

## Introduction

### Background

Tobacco use remains a global public health concern; annually it causes 6 million preventable deaths [1]. The tobacco consumption epidemic is shifting to low- and medium-income countries (LMICs) such as some countries in the Latin American and Caribbean (LAC) region [2]. Currently, more than 120 million smokers live in these countries [3]; half of them will develop a tobacco-related disease and consequently will require medical care.

In the LAC region, smoking rates vary by country, sex, and socio-economic status [4,5]. In some low-income countries, such as Bolivia, Guatemala, and Paraguay, smoking rates are 10 percentage points higher than the rest of the LAC countries [6]. Thus, among men, smoking prevalence ranges from 42% (in Bolivia) to 22.9% (in Paraguay) [7]. Among women, the prevalence is lower, but it is rapidly increasing, confirming the alarming feminization of the epidemic in LAC countries [7]. In the overall region, smoking-related mortality accounts for 16% of total mortality [7], and according to the World Health Organization (WHO), smoking-related deaths will increase by 700% by 2030 [8]. The report points out that the epidemic can be curbed by implementing comprehensive tobacco control measures embraced by the WHO Framework Convention on Tobacco Control (WHO-FCTC) [9]. These measures have demonstrated the reduction of tobacco use and the increase of awareness of its hazards [9]. Guatemala, Paraguay, and Bolivia signed the WHO-FCTC early on, and have implemented some tobacco control measures, including smoke-free legislation (according to the WHO-FCTC Article 8) in workplaces and public places, including health care services. However, smoking cessation services (Article 14) have not received the same recognition and attention [5]. As a consequence, smoking cessation interventions are not well spread among health care services within these countries. Smokers are frequent users of health care services, and their contact with the health system might be an adequate “teachable moment” for quitting [10]. Indeed, according to studies conducted in the United States between 60% and 70% of patients make an attempt to quit while they are hospitalized [11]. However, in spite of these favorable conditions, evidence-based cessation programs are hardly available in LAC countries [12]. The most common barriers to incorporating tobacco cessation interventions into hospitals involve lack of training, expertise, and time. In addition, organizational and financial constraints threaten the suitability of smoking cessation interventions [6].

In LAC countries smoking consumption among health care professionals is still similar to that of the general population [13,14], and most doctors and nurses acknowledge that they have not received formal training in smoking cessation during their undergraduate or graduate training [14]. Generally, they state little confidence in its effectiveness to help their patients to stop smoking. Training facilitates having a more positive attitude on smoking cessation [15] and helps to increase the performance of smoking cessation interventions [16]. Given that about 70% of smokers visit health services over the course of a year, the lost opportunities to intervene remain significant [3]. Frequently, providers believe that smoking cessation is extremely important, but also extremely difficult due to a serious communication gap between doctors and patients that jeopardizes the opportunities to support smokers to quit [17].

Implementation research recommends addressing organizational constraints in order to overcome executive barriers when the cessation messages are delivered such as lack of time, support, and resources [18,19]. Training programs obtain higher impact and sustainability when they are fostered by organizations that allocate time, promote key champions, and provide implementation materials and resources [20,21]. At the organizational level, the chief executive should endorse the initiative and disseminate this endorsement through senior management meetings and routine communication mechanisms. In addition, an implementation committee led by a champion and members of the executive board should establish a feasible execution plan. Following this strategy, tobacco cessation training programs would better sway professional norms and promote the implementation of smoking cessation services.

In the literature, there are several conceptual training models that exhibit significant heterogeneity [22]. For example, online courses allow for distance-learning, are cost-efficient, and provide modes to teach and reinforce counseling skills that often can be difficult to convey in traditional classroom settings [23,24]. Moreover, online training has clear potential to meet large-scale training dissemination needs. Compared with classroom instruction, online training offers greater learner accessibility, increased convenience, and greater scalability [22]. Previous online tobacco cessation training courses have demonstrated an increase in the health provider's skills to counsel patients on tobacco cessation [16,25,26]. Although there are several distant learning tobacco cessation training programs the majority have been developed and evaluated in English-speaking countries. A recent review on online tobacco dependence treatment training programs (all in English) found that 17 out of the 24 courses evaluated failed to meet minimal quality standards. The authors suggested improving instructional design elements, such as teaching effectiveness, learning strategies, instructor’s role and assessment, and evaluation [27].

Using previously established programs can save time and money while increasing the likelihood of achieving successful outcomes [27]. In addition, research training initiatives have been suggested to increase capacity-building efforts, in particular within developing countries [22]. However, the evidence of distant learning training from high-income countries (HICs) may not be directly applicable to LMICs and may need cultural and content adaptations. Research is needed to develop and understand how best to implement effective smoking cessation strategies in LMICs, especially in resource-poor environments where access to health care providers are limited.

### Conceptual Framework

Adaptation implies not only to the replication or translation of a program but to the process of adjusting a program to reduce mismatches between its characteristics and the new context in which it is to be implemented. Adapting a tobacco cessation education program should take into account the treatment regulation of each country, the existing guidance and proceedings, and the dynamics of the health organization [3]. Card et al [28] propose science-based pragmatic steps to adapt an existing program to new contexts based on the following steps: (1) select a suitable, effective program; (2) gather the original program materials; (3) develop a program model; (4) identify the program score components and best-practice characteristics; (5) identify and categorize mismatches between the original program model or materials and the new context; (6) adapt the original program model, if warranted; and (7) adapt the original program materials. To fill the gap of the lack of tobacco cessation training programs in Spanish-speaking LAC countries, we designed the “Fruitful study.”

### Prior Work

We selected the ongoing Brief Intervention for Smoking Cessation Training Program from the Catalan Institute of Oncology (ICO) as the baseline program and created a partnership between ICO and three hospitals from Bolivia, Paraguay, and Guatemala to first adapt and later disseminate the course. We intend to increase the capacity-building of the implicated organizations that will ultimately initiate a cascade of change within their countries [29]. Our training is intended to be a vehicle for the systematic dissemination of the clinical practice guidelines for treating tobacco dependence in hospitalized and ambulatory smoker patients.

The purpose of this paper is to describe the methodology and evaluation strategy of the Fruitful Study research protocol intended to adapt, implement, and test the effectiveness of an online, evidence-based tobacco cessation training program addressed to health professionals from Bolivia, Guatemala, and Paraguay.

### Research Objectives

The primary research goal of the Fruitful Study is to evaluate the impact of an online, evidence-based tobacco cessation training program aimed to increase smoking cessation knowledge, attitudes, self-confidence, and performance interventions among health care professionals of three Spanish-speaking low- and middle-income LAC countries (Bolivia, Guatemala, and Paraguay).

### Hypothesis

Our primary hypothesis is the participants in the online tobacco cessation training program will increase their tobacco-related knowledge, attitudes, and behaviors by the 6-month follow-up, as compared to baseline conditions prior to the training. Our secondary hypothesis is that participating hospitals will exhibit greater tobacco control progression, commitment, and implementation of tobacco cessation services.

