#### Implementation Plan

This study is expected to last 24 months (from November 2014 to November 2016). Information on the various activities is depicted in the event planning timeline (Figure 3).

This paper was written during the 18th month of the study when the post-evaluation data was being gathered. During the training (months 6 to 13), each participant had 1 month to fill in the baseline evaluation, complete the online training, and take the exam. Participants were monitored by local coordinators that acted as champions and encouraged participants to enroll and complete the course. Coordinators set monthly meetings with personnel from the different units and services to increase the number of participants and support those enrolled to complete the course. In addition, during the implementation, coordinators from each hospital offered assistance to students with little or no computer skills. Technical support was mainly used by less educated health professionals (assistants and support health professionals) and older workers who were less familiar with the use of computers. They offered their assistance in logging into the online platform, filling out the questionnaires, completing the evaluation, as well as other technical support-related issues. Participants’ progress was monitored in real-time on the Web platform. The project coordinator at the ICO sent biweekly reports of the participants' progress to coordinators, and if necessary personal emails and videos that motivated the students to finish the course and complete the evaluations. Participants accessed the course using their electronic devices (mobile phones, tablets or computers) or the ones provided by their hospitals during and after working shifts. The hospitals from Guatemala and Paraguay made a library available with computers to facilitate students’ enrolment before or after their working hours. The hospital from Bolivia provided a computer room in which students had access to the course and the support of a technician during specific hours of the day. Therefore, the participating hospitals facilitated computer and Internet access at the workplace.

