Trainers’ attitudes, knowledge, and behaviors will be assessed using a questionnaire composed of 63-items. The website-delivered questionnaire is emailed to the participants at baseline and 3 months after finishing the training. The questionnaire, designed by Sheffer et al [40], takes 30 to 40 minutes to complete. The questionnaire gathers information about the provider's sex, tobacco use history, previous tobacco cessation education, level of pro-activity addressing tobacco use, and perceived success in helping patients stop using tobacco [40]. Perceived knowledge and attitudes about treatment of tobacco use will be determined by assessing the levels of (1) motivation; (2) knowledge about tobacco cessation; (3) self-efficacy; (4) importance of providing tobacco use interventions; (5) effectiveness of interventions; (6) importance of barriers; (7) readiness; and (8) level of tobacco cessation intervention provided assessed by the 5A’s model, an evidence-based framework that helps health professionals to structure smoking cessation interventions by identifying all smokers and offering support to help them quit. The 5A's model consists of 5 components: ask, advice, assess, assist, and arrange follow-up. All items are assessed on a discrete scale from 0 (none or not at all) to 10 (the most possible). The pre-test will be administered immediately prior to the training. The post-training assessment is composed of a 37-item questionnaire assessing providers’ knowledge, attitudes, and behaviors, as assessed in the pre-test.

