### Sample Size

Based on literature regarding gains of training [27,40], we anticipate an increase of 40% in health professionals’ level of knowledge, attitudes, and perception in tobacco cessation from baseline to 6 months. Given this estimate, we will need a minimum of 43 participants per hospital, (total 129, alpha=.05, beta=.1, and 15% dropouts). However, we expect at least an overall enrollment of 300 professionals (100 per hospital).

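### The primary hypothesis and sample size refer to 6 months, but the only stated schedule for the trainee questionnaire puts the post-test about 4 months after baseline at most

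*Protocol article*

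**What the plan says.** Three sections of the protocol article fix the timing of the trainee outcome, and a fourth fixes the length of the course.

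- **Hypothesis.** The primary hypothesis is that participants improve in knowledge, attitudes and "behaviors by the 6-month follow-up, as compared to baseline conditions prior to the training".
- **Sample Size.** The calculation assumes a 40% increase in the "level of knowledge, attitudes, and perception in tobacco cessation from baseline to 6 months".
- **Instruments, Tool 2.** "The website-delivered questionnaire is emailed to the participants at baseline and 3 months after finishing the training". The baseline is placed close to the course: "The pre-test will be administered immediately prior to the training". One follow-up is described: "The post-training assessment is composed of a 37-item questionnaire assessing providers’ knowledge, attitudes, and behaviors, as assessed in the pre-test".
- **Implementation Plan.** Training ran in study months 6 to 13, and "each participant had 1 month to fill in the baseline evaluation, complete the online training, and take the exam".

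No section of the text describes a second post-training questionnaire or one sent at 6 months.

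**The concern.** The Hypothesis and Sample Size sections name a 6-month outcome, while the section that says how that outcome is collected gives a different and earlier date. Followed as written, the schedule does not test the hypothesis as written.

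This matters because the study is an uncontrolled pre-post comparison. With no concurrent group, the interval between the two questionnaires is part of the definition of the effect. The article gives no information on how gains change between 3 and 6 months, so a result from the earlier date cannot stand in for the later one. If the summative paper carried over the 6-month label from the hypothesis while using data collected as Instruments describes, readers would credit the course with a durability that had not been observed.

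**Working it through.** **The plan's own figure.** Sample Size gives 43 per hospital and 129 in total, with alpha 0.05, beta 0.1 and 15% dropout.

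- Total: 3 × 43 = 129, which agrees.
- Dropout: N = n / (1 − 0.15). With n = 36, 36 / 0.85 = 42.4, rounded up to 43. So about 36 evaluable per hospital are implied.
- The 36 cannot be derived from the stated inputs, because no baseline level, standard deviation or sidedness is given and the 40% is not identified as absolute or relative. It can be reached under assumptions:
  - Two proportions, assumed 30% to 70%, two-sided: n = [1.96·√(2·0.5·0.5) + 1.2816·√(0.3·0.7 + 0.7·0.3)]² / 0.4² = (1.386 + 0.831)² / 0.16 = 30.7, or 31. The continuity correction raises this to 36, and dropout to 43. Without the correction, 31 / 0.85 gives 37.
  - Paired proportions (McNemar), assumed discordance 0.60 and difference 0.40, two-sided: n = [1.96·√0.60 + 1.2816·√(0.60 − 0.16)]² / 0.16 = (1.518 + 0.850)² / 0.16 = 35.1, or 36, then 43.

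The 43 is therefore neither confirmed nor shown to be wrong. Time does not appear in either formula. A change of time point affects N only through the assumed gain or dropout.

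**Timing for one participant.**

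| Quantity | Value | Source |
|---|---|---|
| Baseline to end of course | at most 1 month | Implementation Plan |
| End of course to post-test | 3 months | Instruments, Tool 2 |
| Baseline to post-test | at most 1 + 3 = 4 months | sum |
| Stated primary horizon | 6 months | Hypothesis; Sample Size |

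- Origin at baseline: 6 − 4 = 2 months short.
- Origin at end of training: 6 − 3 = 3 months short.

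Neither origin gives 6 months.

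**Study calendar.** Training ended in month 13. The last 3-month questionnaire was due at about month 13 + 3 = 16, and a 6-month one would have been due at about 13 + 6 = 19. The Implementation Plan states: "This paper was written during the 18th month of the study when the post-evaluation data was being gathered". The Results section has evaluations ending in November 2016, about month 24. Collection in month 18 fits a 6-month questionnaire for the last trainees. It also fits late replies to a 3-month one, or the hospital audit and qualitative work. The calendar does not decide between the two figures.

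**The case against.** - **The hypothesis says by, not at, the 6-month follow-up.** An earlier measurement could loosely fall under that wording. But the sentence names a follow-up that the schedule lacks, and Sample Size speaks of change from baseline to 6 months. The loose reading does not reconcile the sections.
- **An article condenses the full protocol.** That would excuse missing detail such as response windows, whose absence is not at issue here. It does not excuse two incompatible dates that are both printed.
- **Figure 3, the event timeline, is not shown.** This stands as a limit. A 6-month administration there can be neither confirmed nor excluded. If it did appear, Instruments would still disagree with it.
- **Instruments dates the email, not the reply.** This also stands: some replies could arrive near 6 months. To reach 6 months from baseline, however, a participant would have to answer about 2 months or more after the email was due, and that is not a planned time point.

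Two stronger readings are tempting but not supported. A reader might infer that the 6-month point is never measured. That holds only for the schedule as written in the text, with the figure unseen and reply dates unknown. A reader might also infer from the calendar that actual lags ran from 3 to about 11 months (month 13 to month 24), leaving the pooled change with no defined time point. That assumes all evaluation up to month 24 is this questionnaire, although the study also has a post-training audit, focus groups and interviews. It also counts only from the last training month and ignores those who finished earlier. The documents do not establish any such spread.

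**Conclusion.** The article contradicts itself on the time point of its primary outcome. As scheduled in the text, the post-test is due at most about 4 months after baseline, against a stated 6: a gap of 2 months from baseline or 3 months from the end of training. This rests on the 1-month course allowance and the 3-month email date both being as printed.

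The documents do not show whether 3 or 6 months is the slip, nor that a 3-month result will be reported as a 6-month one. The contradiction does not make the sample size wrong, since 43 per hospital does not depend on the time point by itself. The correction costs little, but it concerns the primary hypothesis and should be made before the summative results are reported.

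**What to change.** Make the Hypothesis, Instruments and Sample Size sections agree on one primary time point, and say whether it is counted from baseline or from the end of training.

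- **If the questionnaire was sent as Instruments states:** restate the hypothesis and the sample-size paragraph as the change from baseline to 3 months after finishing the training. Do not describe the result as a 6-month effect. Confirm that the assumed 40% gain and 15% dropout are still meant for that date; if so, 43 per hospital and 129 in total remain.
- **If it was in fact sent at 6 months:** correct Instruments and state the origin.
- **In either case:** report the actual time from finishing the training to response. The questionnaire is delivered through a website and progress was followed on the web platform, so the dates should be available; this is an assumption, as the article does not say that they are stored.

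Adding a new 6-month mailing is not a general remedy. The article was written in month 18 with training complete, so anyone who finished before about month 18 − 6 = 12 had already passed 6 months.

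The cost is a wording change and one descriptive summary of response times. The downside of the first route is a shorter-term claim.
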